### 1.2. Aim and Objectives

The aim of this study is to develop and theoretically justify a comprehensive, 12-week integrated dance-mindfulness protocol grounded in polyvagal theory, motor learning science, and embodied phenomenology. The protocol systematically operationalizes the cultivation of nervous system resilience, technical dance competence, authentic creative expression, and social belonging within structured modern dance theater (Imperial Society of Teachers of Dancing-ISTD syllabus [26]) for community-based adult dancers. The study investigates whether this integrated protocol produces measurable psychological improvements compared to standard dance instruction, and whether participants report enhanced embodied meaning-making and somatic awareness through phenomenological accounts. The specific objectives are:(1)To develop and operationalize a comprehensive, 12-week integrated dance-mindfulness protocol grounded in neuroscience, motor learning, and embodied phenomenology that systematically integrates theory with practice.(2)To evaluate the protocol’s effectiveness using a mixed-methods RCT design comparing intervention and control groups on quantitative and qualitative outcomes.(3)To evaluate the intervention’s effectiveness on psychological well-being and embodied experience.

Based on the theoretical framework and structure of the 12-week intervention, it is hypothesized that participants in the dance mindfulness intervention group will demonstrate significantly greater improvements than those in the control group across primary quantitative outcomes (life satisfaction, subjective happiness, psychological distress, mindful attentional capacity, and leisure involvement) and secondary qualitative outcomes (enhanced somatic awareness, nervous system resilience, technical confidence, creative expression, relational belonging, social connection and embodied meaning-making).

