### 2.4. Sample Size and Recruitment

To determine the appropriate sample size for this study, a power analysis was conducted using GPower 3.1 software [32]. The analysis was based on a repeated-measures design with two groups (experimental and control), with measurements taken at baseline and post-intervention. The following parameters were used: Effect Size (Cohen’s d) = 0.50 (medium effect); Alpha Level (α) = 0.05 (5% significance threshold); Power (1 − β) = 0.80 (80% probability of detecting a true effect); two measurement time points (pre- and post-intervention); and two groups (experimental and control). According to the power analysis, the minimum sample size required to achieve sufficient statistical power is 114 participants, with 38 participants in the control group and 76 in the experimental group.

Participants will be informed about the study through targeted outreach at private recreational dance schools in four cities (Larissa, Trikala, Karditsa, Kalampaka) within the Thessaly region, Greece, with an estimated 1–2 participating schools across these cities. Recruitment methods include flyers, posters, verbal announcements during dance classes, and direct recruitment by dance school directors. Recruitment occurs over an anticipated 1–2 month period, with baseline assessments completed by the end of Month 2. During initial contact, prospective participants receive a participant information sheet detailing study aims, procedures, risks, benefits, confidentiality protections, and withdrawal rights. The information sheet describes the study as “a 12-week integrated modern dance program” without mentioning mindfulness components, to minimize selection bias toward mindfulness-seeking participants. Individuals expressing interest undergo preliminary telephone or in-person screening with a trained site coordinator to assess adherence to inclusion and exclusion criteria (Section 2.3). Those meeting preliminary eligibility criteria are informed of the next steps. Individuals with intense mental health distress or active engagement in concurrent mindfulness-based interventions are offered future participation following symptom resolution or completion of conflicting interventions, rather than immediate exclusion.

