### 2.7. Data Collection and Analysis

Self-report questionnaires (SWLS, DASS-21, MAAS, SHS, LIS) are administered on paper at baseline (T0) and post-intervention (T2) by trained site coordinators in quiet studio environments (~20–30 min per assessment). Questionnaires are entered into a secure electronic database with double-entry verification.

Demographic and baseline characteristics are summarized using descriptive statistics (means, standard deviations, medians, frequencies, percentages). Shapiro–Wilk tests and visual inspection (Q-Q plots, histograms) assess normality for all primary outcome variables. Between-group demographic comparisons use independent-samples *t*-tests (continuous) and chi-square tests (categorical). Internal consistency is assessed using Cronbach’s alpha (α ≥ 0.70); test–retest reliability via intraclass correlation coefficients (ICC ≥ 0.70) in the control group.

If normality is met (Shapiro–Wilk *p* > 0.05), a 2 (Group) × 2 (Time) mixed-model repeated-measures ANOVA is conducted on each primary outcome, with Bonferroni-corrected α = 0.01 to control Type I error. Alternative testing via MANOVA (Wilks’ Lambda, α = 0.05) proceeds to univariate ANOVAs if significant. ANCOVA with T0 baseline covariates is conducted with Levene’s test assessing homogeneity of variance; if violated (*p* < 0.05). Effect sizes and 95% confidence intervals are reported.

If normality is violated (Shapiro–Wilk *p* < 0.05), non-parametric tests will be used: Friedman’s test (within-group time effects), Mann–Whitney U (between-group comparisons), Wilcoxon signed-rank test (within-group pre–post). Post hoc pairwise comparisons use Bonferroni-corrected alpha. Pearson correlations (Bonferroni-corrected) for normally distributed variables; Spearman’s rank-order correlations for non-normal variables. Correlations ≥ |0.30| are highlighted. Quantitative analyses use IBM SPSS v. 28; results are reported per CONSORT guidelines [31] with summary statistics, 95% confidence intervals, and effect sizes. Significance level: α = 0.05 (two-tailed) unless otherwise specified (Bonferroni-corrected α = 0.01).

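### Section 2.7 implies a lead test for the five primaries but adds a MANOVA route and an ANCOVA with no trigger, deciding role or alpha; ANCOVA on T0 should be the single confirmatory test

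*Protocol article*

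**What the plan says.** Section 1.2 names five "primary quantitative outcomes (life satisfaction, subjective happiness, psychological distress, mindful attentional capacity, and leisure involvement". Section 2.7 splits the analysis by a Shapiro-Wilk test. Where normality is met, three procedures are applied to these outcomes:

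1. A 2 × 2 "mixed-model repeated-measures ANOVA is conducted on each primary outcome, with Bonferroni-corrected α = 0.01 to control Type I error".
2. "Alternative testing via MANOVA (Wilks’ Lambda, α = 0.05) proceeds to univariate ANOVAs if significant". No condition says when this replaces the first procedure, and the univariate follow-ups have no alpha of their own.
3. "ANCOVA with T0 baseline covariates is conducted with Levene’s test assessing homogeneity of variance; if violated". The sentence ends after the p-value that defines the violation and gives no action. No alpha or rank is given for the ANCOVA.

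Outcomes that fail Shapiro-Wilk go to Friedman, Mann-Whitney and Wilcoxon tests instead. The section closes with a default: "Significance level: α = 0.05 (two-tailed) unless otherwise specified (Bonferroni-corrected α = 0.01". Section 2.4 states that randomization, 2:1, follows completion of the T0 assessment.

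**The concern.** Within the normality-met branch, each primary hypothesis can be tested in three ways under alpha rules that are not aligned, and no sentence says which p-value settles it. Shapiro-Wilk chooses between parametric and non-parametric tests but not among these three.

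Two things are at stake. The first is the claimed Type I control. A significant MANOVA protects the follow-up tests only when all five nulls are true. Once one outcome has a real effect the gate tends to open, and the remaining null outcomes are tested at whatever alpha the follow-ups carry. That situation is plausible here, since a mindfulness programme might move the mindfulness scale and leave life satisfaction or leisure involvement unchanged. The second is power. The implied lead test discards information that the ANCOVA already in the plan would use.

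**Working it through.** **Inputs from the article.** Five primaries (Section 1.2); 38 control and 76 intervention; "Effect Size (Cohen’s d) = 0.50 (medium effect"; "Alpha Level (α) = 0.05 (5% significance threshold"; "Power (1 − β) = 0.80 (80% probability of detecting a true effect" (Section 2.4); 0.01 per primary for the RM-ANOVA and a 0.05 two-tailed default (Section 2.7). **Assumed, because the article does not give them:** pre-post correlation r, and correlation between outcomes.

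**The plan's own figure.** With d = 0.50, power 0.80 and 2:1 allocation, a two-sample t-test at one-sided 0.05 needs 38 + 76 = 114 (power 80.4%). At two-sided 0.05 it needs 48 + 96 = 144. The stated 114 is therefore reproduced, but as a one-sided calculation at 0.05. That is a separate sample-size matter and adds no weight here. The check below takes 76:38 as given.

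**Step 1: false claims on the MANOVA route.** Five outcomes were simulated at 38/76, with the MANOVA (Hotelling's T²) on change at 0.05 as a gate, followed by univariate tests of change. One outcome has a true effect and four are null. Entries are the chance of at least one false claim among the four, from 8,000 trials per row at r = 0.5:

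| Between-outcome correlation | True effect on one outcome | Follow-ups at 0.05 | Follow-ups at 0.01 |
|---|---|---|---|
| 0.3 | d = 0.5 | 14.5% | 3.9% |
| 0.3 | d = 0.8 | 17.2% | 4.1% |
| 0.5 | d = 0.5 | 14.2% | 3.3% |
| 0.5 | d = 0.8 | 15.3% | 3.4% |

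A separate run of 4,000 trials per row at follow-up 0.05 gave 14.5%, 16.3%, 12.6% and 14.7% in the same order. Together these give about 13-17% at 0.05 and about 3-4% at 0.01. As a cross-check, the limit for four independent nulls with the gate always open is 1 − 0.95⁴ = 18.5% at 0.05 and 1 − 0.99⁴ = 3.9% at 0.01. If all five nulls are true, the gate holds the route with 0.05 follow-ups at 4.2-4.7% (correlations 0 to 0.5).

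**Step 2: RM-ANOVA against ANCOVA, outcome by outcome.** With two time points, the Group × Time F-test is the square of the t-test on change. Taking the T2 variance as 1, equal variances and a common slope:

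- variance factor for change: 2(1 − r)
- variance factor for ANCOVA: 1 − r²
- ratio ANCOVA/change: (1 − r²) / [2(1 − r)] = (1 + r)/2

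The noncentrality is [0.5 / √(variance factor)] × √(38 × 76 / 114), and √(38 × 76 / 114) = 5.033. The two-sided 0.01 critical value is 2.62 (112 df for change, 111 for ANCOVA).

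| r | Factor, change | Noncentrality | Power | Factor, ANCOVA | Noncentrality | Power | Variance ratio |
|---|---|---|---|---|---|---|---|
| 0.5 | 1.00 | 2.517 | 46% | 0.75 | 2.906 | 61% | 0.75 |
| 0.6 | 0.80 | 2.814 | 58% | 0.64 | 3.146 | 70% | 0.80 |
| 0.7 | 0.60 | 3.249 | 73% | 0.51 | 3.524 | 81% | 0.85 |

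**Step 3: familywise error with one test per primary.** Five tests at 0.01 give at most 5 × 0.01 = 0.05 (1 − 0.99⁵ = 4.9% if independent).

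**The case against.** **There is a lead test.** A reader might infer that Section 2.7 has no hierarchy at all. It does imply one: only the RM-ANOVA is tied to each primary outcome with an explicit 0.01, and the MANOVA is labelled an alternative. This objection stands. What is missing is narrower: the trigger for the alternative, the role and alpha of the ANCOVA, and a statement of which result decides.

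**The follow-ups may already be at 0.01.** A reader might also infer that the MANOVA route definitely evades the 0.01 rule. The text does not settle this. Its 0.05 is attached to Wilks' Lambda, and the sentence before sets 0.01 for ANOVAs on the same outcomes. On that reading the error is about 3-4% and there is no inflation. The 0.05 default supports the other reading, so the 13-17% is conditional.

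**RM-ANOVA is valid.** It is a legitimate analysis of a randomized pre-post design, so preferring ANCOVA is a matter of efficiency and not a correction of an error. Nor is ANCOVA superior in every case. With 2:1 allocation and different slopes by arm, common-slope ANCOVA can lose: slopes of 0.5 (intervention) and 1.1 (control) gave simulated variances of 0.0244 for ANCOVA and 0.0230 for change. That is an edge case. MANOVA tests an omnibus hypothesis and does not belong in the power comparison.

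**Condensed article.** The Levene sentence may have lost text in publication. That justifies a request to complete it, not a claim that no action was planned.

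What survives is the missing decision rule. The article itself names the three tests under different alpha rules, so this is not simply detail left to an unseen analysis plan.

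**Conclusion.** The point holds in limited form. RM-ANOVA at 0.01 is the implied lead, but the plan leaves open when the MANOVA route replaces it, what alpha the follow-ups and the ANCOVA carry, and which result decides each primary.

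The familywise risk on the MANOVA route is about 13-17% if the follow-ups use 0.05 and about 3-4% if they use 0.01. Both figures assume that one of five outcomes truly differs (d = 0.5-0.8) and that outcomes correlate at 0.3-0.5. One could go further and compute the error from picking the best of all three routes with ANCOVA at 0.05. With all nulls true that gives 20-23% in simulation (between-outcome correlation 0 to 0.5). It is a worst case only, because the article neither assigns ANCOVA 0.05 explicitly nor says that the most favourable result will be used.

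The efficiency loss from leading with RM-ANOVA is 8 to 15 percentage points of power at two-sided 0.01 and d = 0.5, for assumed r between 0.7 and 0.5, under a common slope and equal variances. Confidence is high on the missing decision rule. The size of the power gain depends on a pre-post correlation that the article does not report.

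**What to change.** By a dated amendment made before outcome data are analysed:

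- Name one confirmatory test for each of the five primaries: ANCOVA of the T2 score on arm, with the same scale's T0 score as covariate. Test at two-sided 0.01 each, or by Holm at a familywise 0.05, and report the adjusted difference with its confidence interval.
- Apply it whatever the Shapiro-Wilk result. Otherwise the normality branch would still divert outcomes to a different deciding test.
- Label RM-ANOVA, MANOVA with its follow-ups, and the non-parametric tests as supportive, with no claim resting on them.
- Complete the Levene sentence by stating the action if homogeneity is violated. Robust standard errors are one option, and the rest of the fix does not depend on that choice.

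If the sponsor prefers to keep RM-ANOVA as the deciding test, the minimum is to say so, give the MANOVA trigger and a follow-up alpha of 0.01 (or make it descriptive), and give the ANCOVA a role and an alpha.

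The cost is a documented amendment. No further participants or measurements are needed, because T0 is collected on everyone before randomization. Section 3 schedules data collection from early January to early April 2026, so the date and justification of the change must be recorded.

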## 2. Experimental Design

### 2.1. Trial Design

This study has been prospectively registered on ClinicalTrials.gov (NCT07262177; brief title: Dance-Mindfulness Intervention for Well-Being in Recreational Adults-DanceMind) and approved by the institutional Research Ethics Committee (IEC, DPESS, UTH 4-2/2.4.2025; Supplementary File S8 [27]). The protocol follows SPIRIT [28,29], TIDieR [30], and CONSORT standards [31].

This is a two-parallel group randomized controlled trial (RCT). The intervention group receives a 12-week integrated dance-mindfulness protocol grounded in polyvagal theory, motor learning science, and embodied phenomenology. The control group continues regular recreational dance activities without mindfulness or somatic-reflective components. Participants are randomly allocated 2:1 (intervention: control) using computer-generated randomization with allocation concealment.

Quantitative assessments occur at baseline (T0) and post-intervention (T2 Week 12). Qualitative data collection occurs at mid-intervention (T1 Week 8) and post-intervention (T2 Week 12). This mixed-methods design permits concurrent testing of quantitative psychological outcomes (life satisfaction, subjective happiness, psychological distress, mindful attention, leisure involvement) and qualitative embodied experiences (somatic awareness, nervous system resilience, technical confidence, creative expression, relational belonging, meaning-making).

All procedures follow ethical principles outlined in the Declaration of Helsinki. Written informed consent is obtained prior to enrollment. Participants have the right to withdraw at any time without consequence. Personal data are stored securely in encrypted databases. Each participant receives a unique study code; identifying information is separated from research data. All facilitators hold CPR/First Aid certification and mindfulness training. Session checklists document adverse events. If a participant reports intense psychological distress, the study is suspended for that individual with clinical referral provided. Facilitators are trained to recognize signs of emotional dysregulation and provide immediate basic containment (quiet space, grounding breath), without attempting psychological exploration. Control group participants receive delayed access to the intervention after post-intervention assessment (Supplementary Files S1–S8 [27]).

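### In the parametric branch, pooled-variance ANOVA and ANCOVA at 76/38 are miscalibrated if the arms' spreads differ, and the only variance check leads to no action

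*Protocol article*

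**What the plan says.** Section 2.1 fixes unequal allocation: "Participants are randomly allocated 2:1 (intervention: control) using computer-generated randomization with allocation concealment". Section 2.4 gives the resulting arms: "114 participants, with 38 participants in the control group and 76 in the experimental group".

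For outcomes that pass Shapiro–Wilk, section 2.7 states that a 2 × 2 "mixed-model repeated-measures ANOVA is conducted on each primary outcome, with Bonferroni-corrected α = 0.01 to control Type I error". It adds MANOVA followed by univariate ANOVAs as an alternative, and an ANCOVA on baseline. Effect sizes and 95% intervals are to be reported, with no form of standard error named.

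Unequal variance appears once, in the ANCOVA sentence: Levene's "test assessing homogeneity of variance; if violated". A threshold of p < 0.05 follows and the sentence stops. Outcomes that fail Shapiro–Wilk go to rank tests, with Mann–Whitney between groups. That switch responds to non-normality, not to unequal spread.

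**The concern.** With two time points, the group-by-time F test is the square of a pooled-variance t test on change scores. The ordinary ANCOVA also uses a single residual variance. With equal arms such tests tolerate unequal spread well; with a 2:1 split they do not. The pooled estimate is dominated by the 76, while the true standard error depends most on the 38.

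The article states a condition for this problem but no response to it, and only for the ANCOVA. As written, the analyst would choose the response after seeing Levene's result. At stake are interval coverage, the error rate of tests of the mean difference when response varies between people, and power.

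**Working it through.** **Inputs.** 76 and 38 participants and d = 0.50 (section 2.4); two-tailed 0.05, or 0.01 for each primary outcome (section 2.7). No SD is given for either arm, so the ratio k = intervention SD / control SD is an assumption, shown as a range.

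**The plan's own figure.** For a two-sample comparison at 2:1, the control arm is 1.5 × (z_α + z_β)² / d². One-sided at 0.05 this is 1.5 × (1.645 + 0.842)² / 0.25 = 37.1, so 38 and 76, total 114 (exact-t power 0.804). The stated total is reproduced, on a one-sided test; two-sided gives 48 and 96, total 144. That mismatch with the two-tailed analysis is a separate matter. Here 114 only fixes the arm sizes.

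**Standard error.** With control SD = 1:
- true SE = √(k²/76 + 1/38)
- pooled SE ≈ √[ (75k² + 37)/112 × (1/76 + 1/38) ]

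At k = 0.80, pooled/true = √(0.7589 × 0.03947) / √(0.00842 + 0.02632) = 0.1731/0.1864 = 0.93, so 7% too small. At k = 1.25 the ratio is 1.08, so 8% too large.

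**Error rates under equal means.** Simulated normal data, 76/38, pooled t on change scores, at least 200,000 runs per row:

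| k | error at 0.05 | error at 0.01 | 95% coverage |
|---|---|---|---|
| 0.67 | 0.085 | 0.024 | 91.5% |
| 0.80 | 0.069 | 0.017 | 93.1% |
| 0.88 | 0.060 | 0.0136 | 94.0% |
| 0.97 | 0.052 | 0.011 | 94.8% |
| 1.00 | 0.050 | 0.010 | 95.0% |
| 1.25 | 0.035 | 0.006 | 96.5% |
| 1.50 | 0.026 | 0.004 | 97.4% |

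Welch stays at about 0.050 and 0.010 in every row. At 57/57 the pooled test stays at 0.050–0.051 over SD ratios from 0.5 to 2, so the distortion comes from the 2:1 split. Ordinary ANCOVA (baseline slope 0.5) behaves alike: at residual-SD ratio 0.80 its error at the 0.01 level is 0.016, against 0.010 with HC3 standard errors.

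**Which ratios are plausible.** Suppose floor compression cuts the intervention arm's post-score SD to k_post times control, with equal baseline SDs, control post SD equal to baseline, and pre–post correlation ρ in both arms. The change-score SD ratio is √[(1 + k_post² − 2ρk_post) / (2 − 2ρ)].
- k_post = 0.80: √(0.84/1.00) = 0.92 at ρ = 0.5; √(0.36/0.40) = 0.95 at ρ = 0.8.
- k_post = 0.67: 0.88 at ρ = 0.5; 0.97 at ρ = 0.8.

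So for change scores the error at the 0.01 level is about 0.011 to just under 0.014. For ANCOVA, the residual SD within an arm is post SD × √(1 − ρ²). With the same ρ the ratio therefore carries over roughly unchanged, and 0.80 is more plausible there.

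**Power at 0.01.** At k = 1.25 and a true difference of 0.5 control SD: pooled 31%, Welch 38%. At k = 1: pooled 46.2%, Welch 45.4–45.5%.

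**Levene as a gate.** At these arm sizes it detects ratios of 0.80 or 1.25 about 30% of the time, and 0.67 or 1.5 about 70–76%.

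**The case against.** The strongest reply is that the magnitude is assumed and the false-positive risk weak. Much of this stands.

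- **No SDs are given.** A reader might infer from the table that the 0.01 tests run at 0.017 to 0.024. The documents do not support that for the change-score analysis. Floor compression shrinks post-score spread far more than change-score spread, as the ratios of 0.88–0.97 show.
- **The strict null is safe.** If the programme changes nobody's outcome, the arms' variances stay equal and the pooled test is valid. Compression arises when the programme works, and the cost is then mainly coverage. Varied response widens the larger arm, so its cost is lost power, not false claims.
- **Not necessarily all five primary outcomes.** A floor-compressed distress score is the one most likely to fail Shapiro–Wilk and go to Mann–Whitney. That test is less distorted, though not immune, and is outside this point.
- **Shared classes are not an argument here.** They create correlation between participants, which neither Welch nor HC3 corrects.
- **A full analysis plan may settle the method.** Silence about variance in the ANOVA or MANOVA of a condensed article is therefore not the defect.

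What does not stand is that completing the sentence would be enough. The article fixes a condition and threshold and then stops, and a finished Levene rule would miss moderate differences about 70% of the time. The method it does name is also the one that 2:1 allocation makes fragile.

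**Conclusion.** The point holds, with modest weight. In the parametric branch of section 2.7, pooled-variance inference at 76/38 is miscalibrated whenever the arms' spreads differ, and the stated check triggers nothing. The likely size is small for change scores under floor compression. It is moderate if ANCOVA residuals differ by a ratio of about 0.80: error near 0.016 at the 0.01 level and 93% coverage. At 1.25 the tests are conservative (about 0.006) and some 7 points of power are given up relative to Welch. These figures rest on normal, independent data, full planned arm sizes and assumed SD ratios. They do not show that the trial's false-positive rate is inflated on every primary outcome.

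**What to change.** Replace the unfinished Levene sentence in section 2.7 with a prespecified rule. For each primary outcome in the parametric branch, the between-arm contrast, its p-value and its 95% interval use unequal-variance inference, whatever Levene's test shows. This means Welch's method on change scores, or ANCOVA with HC3 standard errors. Levene's result may still be reported descriptively.

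The cost is one sentence and a standard software option, with the sample size unchanged. If variances are equal, Welch loses under 1 point of power (46.2% to about 45.5% at the 0.01 level). Correlation within classes and the rank-test branch need their own treatment.

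### When Shapiro–Wilk rejects, the only test left that can answer the between-group hypothesis has no stated variable and no assigned alpha, and it sits beside two within-group tests that cannot answer it

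*Protocol article*

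**What the plan says.** Section 1.2 states a comparative hypothesis: "participants in the dance mindfulness intervention group will demonstrate significantly greater improvements than those in the control group across primary quantitative outcomes". It lists five such outcomes: "life satisfaction, subjective happiness, psychological distress, mindful attentional capacity, and leisure involvement".

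Section 2.7 then makes the analysis depend on the Shapiro–Wilk p-value.

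- **Normality met.** A 2 × 2 "mixed-model repeated-measures ANOVA is conducted on each primary outcome", "with Bonferroni-corrected α = 0.01 to control Type I error". MANOVA and an ANCOVA with T0 covariates are named in the same paragraph, which opens with the normality condition.
- **Normality violated.** The plan states that "non-parametric tests will be used: Friedman’s test (within-group time effects), Mann–Whitney U (between-group comparisons), Wilcoxon signed-rank test (within-group pre–post"). The only multiplicity rule attached to these tests is: "Post hoc pairwise comparisons use Bonferroni-corrected alpha". No divisor is given.

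A closing sentence sets a two-tailed 0.05 as the default unless otherwise specified, with the Bonferroni value of 0.01 in brackets. Section 2.4 gives two time points and 76 intervention against 38 control participants.

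**The concern.** The two branches do not answer the same question in the same way. The first contains a test of the difference in change at a corrected alpha. The second contains two tests that the plan itself labels within-group, plus a Mann–Whitney U with no named variable, no baseline adjustment and no explicit alpha.

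Three things are at stake:

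- the family-wise control claimed for the five primary outcomes;
- freedom to choose between T2 and change after seeing the data;
- the temptation to read significance in one arm but not the other as an effect.

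The switch operates outcome by outcome, so different primary outcomes could be judged by different tests at different alphas.

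**Working it through.** **1. The plan's own alpha.** Five primary outcomes: 0.05 / 5 = 0.01. This reproduces. With five independent tests at 0.01, family-wise error is 1 − 0.99^5 = 0.049.

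**2. Family-wise error if k outcomes switch.** Reading the switched Mann–Whitney tests at the default 0.05 and the others at 0.01, under independence:

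FWER(k) = 1 − 0.95^k × 0.99^(5−k)

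| Outcomes switching | FWER |
|---|---|
| 0 | 0.049 |
| 1 | 0.087 |
| 2 | 0.124 |
| 5 | 0.226 |

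The Bonferroni bound for k = 5 is 5 × 0.05 = 0.25. Positive correlation lowers the error: with all five at 0.05 and a correlation of 0.5, simulation gave 0.18.

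**3. What each substitute test can show.**

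- *Friedman.* With two time points, each participant's ranks are 1 and 2. The statistic therefore depends only on how many went up and how many went down, which is a sign test. It works within a group and adds little to Wilcoxon.
- *Wilcoxon.* Tests pre–post change within one arm, with no comparison between arms.
- *Mann–Whitney U.* Compares the arms. On T2 − T0 it tests the difference in change. On T2 it is a valid test of the arm effect because arms are randomised.

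Mann–Whitney was simulated with 76 against 38, log-normal scores (log-scale SD 0.6), correlations of the underlying normals of 0.5 and 0.7, and 3,000 runs. All of these distributional inputs are assumptions. Under the null it rejected in 0.047–0.057 of runs at nominal 0.05 and in 0.008–0.015 at nominal 0.01. It is therefore close to valid on either variable.

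**4. Does the unnamed variable matter?** In the same simulation, with a true 0.5 SD shift tested at 0.01:

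| Correlation | Power on T2 | Power on change |
|---|---|---|
| 0.5 | 0.76 | 0.65 |
| 0.7 | 0.76 | 0.88 |

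The better choice reverses with a correlation that the document does not give, so leaving it open is a real degree of freedom.

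**5. The within-arm pattern under no group difference.** Assume both arms improve by 0.3 SD, with pre–post correlation r. The SD of change is √(2(1 − r)), and the standardised change is 0.3 divided by that. Paired noncentral-t power at two-sided 0.05:

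| r | SD of change | Power, n = 76 | Power, n = 38 | Intervention only | Control only |
|---|---|---|---|---|---|
| 0.5 | 1.000 | 0.733 | 0.437 | 0.733 × 0.563 = 0.41 | 0.437 × 0.267 = 0.12 |
| 0.6 | 0.894 | 0.823 | 0.522 | 0.823 × 0.478 = 0.39 | 0.522 × 0.177 = 0.09 |
| 0.7 | 0.775 | 0.915 | 0.643 | 0.915 × 0.357 = 0.33 | 0.643 × 0.085 = 0.055 |

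With equal arms the last two columns would be equal, so the imbalance between them comes from the 2:1 allocation. At 0.01 the intervention-only figure is 0.39–0.47, so a stricter alpha does not remove the problem. These are normal-theory figures. The log-normal simulation with Wilcoxon gave 0.23–0.39 at 0.05 and 0.42–0.47 at 0.01.

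**The case against.** A reader might infer that the hypothesis goes untested whenever normality is rejected. The document does not support that: Mann–Whitney U is listed for between-group comparisons, and step 3 shows that it is valid on either T2 or change. Ignoring baseline affects precision, not validity.

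A reader might also infer that this branch is fixed at 0.05. It is not stated. The closing sentence follows both branches and mentions 0.01 in brackets, so 0.05 is the default reading of an ambiguous text. The 23% figure further requires all five outcomes to switch, whereas skew may affect only one or two.

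Nor does the plan say that efficacy will be judged by significance in one arm and not the other. The 33–41% measures how misleading that reading would be; it is not an error rate the plan commits to. Confidence intervals and effect sizes are promised for all quantitative results, so it would be wrong to say that this branch has none.

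An analysis plan, not shown here, might name the variable and alpha. That covers part of the point. But the article itself writes the switching rule, names two within-group tests as substitutes, and attaches Bonferroni only to post hoc comparisons.

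Finally, baseline-adjusted ANCOVA is not always more powerful on skewed data. In the log-normal simulation at 0.01 it had power 0.61 and 0.79 (r = 0.5 and 0.7), below Mann–Whitney on T2 in the first case and below Mann–Whitney on change in both. The case for it is a single prespecified effect estimate for every outcome, not a guaranteed power gain.

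**Conclusion.** The concern holds as a problem of specification and should be fixed. In the non-normal branch, one test of three can answer the hypothesis, and its variable and alpha are not stated. On the default reading, the claimed 5% family-wise control weakens to about 9% with one switched outcome, 12% with two, and 23% at most under independence with all five. The two within-group tests cannot support a comparative claim. Under an assumed equal 0.3 SD improvement with r = 0.5 to 0.7, they would point to the intervention arm alone in about 33–41% of trials at 0.05.

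The 0.3 SD, the correlations, the skewness and the independence of outcomes are assumptions, because the document gives none of them. The family-wise figures also depend on reading the unassigned alpha as 0.05.

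**What to change.** In section 2.7:

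- Replace the Shapiro–Wilk switch with one primary between-group analysis for all five outcomes, whatever the distribution: T2 regressed on arm and T0, with robust or bootstrap intervals, at two-sided α = 0.01.
- If a rank test is wanted, specify Mann–Whitney U on T2 − T0 or a rank-based ANCOVA, also at 0.01, as a sensitivity analysis.
- Remove Friedman.
- Label within-group Wilcoxon results as descriptive and state that they do not bear on efficacy.

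T0 scores are already collected on every outcome, so the cost is wording in the analysis section, with no extra participants or data. The change should be made and dated before outcome data are analysed.
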